#### Interventions

2.5.1

In addition to conventional treatment, patients in the study group will receive acupuncture as adjuvant therapy, which will start within 72 hours after injury or craniotomy; acupuncture will be administered once a day for 28days (a total of 24 treatments with 1 break per week). All interventions will be performed by the same acupuncturist doctor, who has more than 10 years of clinical experience and who will be trained in the study protocol before the start of the trial. Encouragement and supervision from acupuncturists can help improve participants’ adherence.

Only sterile, stainless, disposable acupuncture needles (size: from 0.25 × 30 mm to 0.25 × 50 mm; Suzhou Hwato Acupuncture Medical Appliance Company, China; product no. 20162270970) will be used. In the study group, acupuncture needles will be inserted into acupuncture points located on the midline of the human body (GV20, GV26, and CV9) and on the affected limbs (GB20, GB39, PC6, LI4, ST36, ST40, SP6, KI7, and LR3). If the GV20 point is too close to the surgical site, this acupoint may be skipped. All the acupoints have been selected and localized according to the guideline of WHO Standardized Acupuncture Point Location, and then depending on where the needle is located the insertion depth will be 10 to 40 mm.^[25]^ The needles will be manipulated using twirling, lifting, and thrusting methods to promote Qi. Because patients are not able to express their feelings, eye moisture or the presence of tears will be considered as a kind of Deqi. After insertion, needles will be left in position for 30 minutes in every session and the manipulations of twirling, lifting, and thrusting will be repeated for 1 minute/10 minutes. The location of the relevant acupoints is summarized in Table 1.

**Table 1 T1:** Description of the location of the applied acupoints.

Acupoints	Descriptions
Baihui (GV20)	Straight up 5 cun above the middle of the front hairline
Shuigou (GV26)	At the junction of the upper and middle third of the philtrum
Fengchi (GB20)	Below the occiput, the depression between the upper end of the trapezius muscle and the upper end of the sternocleidomastoid muscle.
Xuanzhong (GB39)	On the outside of the calf, 3 cun above the tip of the lateral malleolus, and the depression of the front edge of the fibula
Shuifen (CV9)	On the upper abdomen, anterior midline, 1 cun above the middle of the umbilicus

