#### Primary outcome

2.6.1

The primary outcome is the functional status of patients with TBE according to a dichotomized GOS (poor recovery = GOS 1∼3; good recovery = GOS 4∼5) at 6 and 12 months after the injury.

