#### Secondary outcomes

2.6.2

The secondary outcomes are wake-promoting rates, changes in the GCS (Baseline GCS is used as the basis for grouping), the volume of TBE calculated by CT scan (i.e., the volume of brain contusions and pericontusional edema), and the serum levels of CRP and IL-6 measured at four different time points (baseline and days 7, 14, and 28 after treatment). Another secondary outcome, the Modified Barthel Index (MBI), will be measured at the beginning of treatment, at the end of 28-day treatment, at the 6-month and 12-month follow-up after injury.

Calculating the volume of TBE, including the volume of brain contusions and pericontusional edema, by CT scan with the help of 3D Slicer software (version 4.8.1) might reduce the subjective impact of quantifying brain edema. 3D Slicer is a free, open source, and multi-platform software package widely used for medical, biomedical, and related imaging research; it has been jointly developed by multiple institutions and has been supported by the National Institutes of Health in the United States.

The Human IL-6 ELISA kit (Wuhan Fine Biotech Co., Ltd., China) or the Human C-Reactive Protein ELISA kit (Head Office in China Beckman Coulter Commercial Enterprise (China) Co., Ltd. Shanghai, China) will be used to determine the concentrations of IL-6 or CRP in the samples, and the data will be analyzed. Collected samples will be centrifuged for 15 minutes at 1000 × *g* and stored in a freezer at −80 C until they are ready for processing and analysis. Samples will be discarded after the analysis. The timepoints for assessment are listed in Table 2.

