### Follow-up

2.7

After 4 weeks of complement acupuncture treatment, the trial will enter a follow-up period till 12 months after injury, when all participants receive the equal therapy as possible follow-up on a monthly basis via telephonic and message communications or outpatient review, treatment compliance and changes of clinical manifestations will be faithfully recorded. The data of 6-month and 12-month will be used for the final statistical analysis of the trial.

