### Sample size calculation

2.9

Because the data available for patients with TBE who receive early acupuncture treatment are limited and inconclusive, we will perform a single-blind RCT in which the control group will receive conventional treatment and the study group will receive additional acupuncture as an adjuvant therapy. The primary outcome will be dichotomized GOS (poor recovery = GOS 1∼3; good recovery = GOS 4∼5) at 6 and 12 months of follow-up after the injury. According to our previous pilot study, the change of GOS (good recovery rate) in the study group was shown to be 80% (n = 12), and that in control group was 50% (n = 12). Sample size was calculated using the Power Analysis and Sample Size (PASS) software package (version 15, NCSS, Kaysville, UT), with a 2-sided significance level (α = 0.05), a power of 80%, and chi-squared tests to assess the difference in rates between the 2 groups. Thus, a total sample size of 80 participants (40 per group) will be recruited, allowing for 10% loss during follow-up.

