### Statistical analysis

2.10

After a patient has been randomly assigned, the outcome measures will be collected even if the trial treatment is interrupted or not given. The data used will include the method of the last observation carried forward or the method of the worst observation carried forward.^[26]^ That is, this study will analyze the data with the full analysis set.

The statistical analyses will be performed by a blinded researcher. According to the intention-to-treat principle, all the data will be analyzed using the SPSS statistical software package (version 20.0, IBM SPSS Statistics, IBM Corp, Somers, NY). Baseline characteristics will be described and compared. Continuous variables subject to normal distribution will be presented as the mean ± standard deviation; continuous variables not subject to normal distribution will be expressed as the median and interquartile range; and categorical variables will be described as the frequency and percentage.

GOS, wake-promoting rates, and adverse events rates will be compared using the chi-squared or Fisher's exact tests. GCS and MBI scores will be compared between the 2 groups by *t* test with a 95% confidence interval. The results of the volume of TBE and the serum levels of CRP and IL-6 between the 2 groups will be compared using either a generalized linear mixed model or the *t* test, and repeated contrast tests will be conducted to account for time differences in each group. If the data are not normally distributed, nonparametric methods will be used. For all analyses, the results with a *P* value less than .05 will be considered statistically significant. The clinical efficacy should be determined in the evaluation of clinical significance.

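### Missing GOS is to be filled by last or worst observation carried forward: the first has no stated GOS to carry at 6 months, and the second, read as worst category, turns unequal loss into an apparent effect.

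*Protocol article*

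**What the plan says.** Section 2.10 (Statistical analysis) first commits to collecting outcomes in every randomised patient, whether or not treatment is given. It then states: "The data used will include the method of the last observation carried forward or the method of the worst observation carried forward". The next sentence treats this as the definition of the analysis population: "That is, this study will analyze the data with the full analysis set". Neither sentence assigns a rule to an outcome or defines worst.

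Section 2.6.1 (Primary outcome) sets the "dichotomized GOS (poor recovery = GOS 1∼3; good recovery = GOS 4∼5) at 6 and 12 months after the injury". Section 2.7 (Follow-up) adds: "The data of 6-month and 12-month will be used for the final statistical analysis of the trial". No part of the text names an earlier GOS. By contrast, section 2.6.2 (Secondary outcomes) schedules GCS, edema volume, CRP and IL-6 at baseline and days 7, 14 and 28. The Modified Barthel Index (MBI) has its own schedule there: it "will be measured at the beginning of treatment, at the end of 28-day treatment, at the 6-month and 12-month follow-up after injury".

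Section 2.9 (Sample size calculation) plans 40 patients per group with 10% loss, from pilot good-recovery rates of 80% and 50%. Section 2.10 compares GOS by chi-squared or Fisher's exact test.

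**The concern.** Two single-imputation rules are joined by an undefined choice, and each has a problem for the primary outcome.

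- **Last observation.** On the text, a patient with no 6-month GOS has no GOS at all to carry. A patient seen at 6 but not at 12 months is assumed not to have changed between the two primary time points.
- **Worst observation.** If this means the worst category, all missing patients become poor recoveries. The analysed rate then mixes recovery with retention, so a difference in retention looks like a difference in recovery. If it means the patient's own worst observed GOS, it has the same gap as the first rule at 6 months.

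The validity of the primary comparison is at stake, and also its power, because worst-category scoring shrinks a true difference even when loss is equal. The sentence is not limited to GOS. Applied to GCS and MBI, carrying forward could give a patient who dies a score recorded while alive.

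**Working it through.** **Inputs from the protocol.** Good recovery 80% and 50%, two-sided α = 0.05, power 80%, 10% loss, 40 per group (section 2.9); 1:1 allocation (section 2.4); chi-squared or Fisher's exact test (section 2.10).

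**Assumptions.** The split of loss between arms (the protocol gives only 10% overall); a common good-recovery rate of 65%, midway between the two pilot rates, with 50% and 80% as a range; loss unrelated to outcome; worst read as worst category.

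**The plan's own figure.** The unpooled two-proportion formula gives n = (1.960 + 0.842)² × (0.8×0.2 + 0.5×0.5) / 0.30² = 35.8, so 36 per arm. Then 36 / 0.90 = 40 per arm, 80 in total. The stated size is reproduced and is not in dispute.

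**What each rule can use for GOS, on the text**

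| Missing visit | Last observation | Own worst observation | Worst category |
|---|---|---|---|
| 6 months | nothing earlier | nothing earlier | poor |
| 12 months, 6-month value known | 6-month value | 6-month value | poor |

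**Worst category, no true effect.** With true rate p and loss d, the analysed good rate is p(1 − d). The apparent difference, study minus control, is p × (d_control − d_study). Rejection rates come from exact binomial enumeration of the uncorrected chi-squared test, 40 per arm, p = 0.65:

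| Loss, study / control | Analysed rates | False difference | Rejection |
|---|---|---|---|
| 10% / 10% | 58.5% / 58.5% | 0 | 5.3% |
| 8% / 12% | 59.8% / 57.2% | +2.6 points | 6.0% |
| 5% / 15% | 61.75% / 55.25% | +6.5 points | 9.5% |
| 15% / 5% | 55.25% / 61.75% | −6.5 points | 9.5% |

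At 5% / 15%, other common rates give:
- p = 0.50: 0.50 × 0.10 = 5.0 points, rejection 8.0%.
- p = 0.80: 0.80 × 0.10 = 8.0 points, rejection 12.3%.

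Fisher's exact test, which the protocol also allows, is conservative: at p = 0.65 and 5% / 15% it rejects in 6.1%. The false difference of 6.5 points is the same.

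**Comparator.** Analysing observed patients only, under the same assumptions, the expected difference is 0 and rejection is 4.5% to 5.3% with 36/36, 38/34 or 40/32 observed.

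**Worst category, true rates 80% and 50%, equal 10% loss.** Analysed rates are 0.80 × 0.90 = 72% and 0.50 × 0.90 = 45%, a difference of 27 points instead of 30. Exact chi-squared power at 40 per arm is 70.9%. The 36 per arm actually observed have 78.7% at 80% versus 50%. The rule costs about 8 percentage points of power.

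**The case against.** **Direction.** A reader might infer that the rule favours acupuncture, because section 2.5.1 (Interventions) says "Encouragement and supervision from acupuncturists can help improve participants" (the sentence goes on to name their adherence), and only the study arm has an acupuncturist. The document does not support that step. The remark concerns adherence to a 28-day treatment, not retention to 6 and 12 months. For the later period, section 2.7 plans monthly contact for all participants, on as equal terms as possible. Reversing the loss reverses the sign.

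**Reading of worst.** The phrase can literally mean the patient's own worst recorded value. The error and power figures above hold only under the worst-category reading. That part stands, but the other reading leaves the 6-month gap unfilled.

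**Size.** About 8 of 80 patients are expected to be lost, and a mild imbalance of 8% versus 12% moves type I error only to 6.0%. Outcomes are to be collected after treatment stops, so stopping treatment need not create missing data. This limits the harm but does not make either rule sound.

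**Open choice.** The statistician is blinded until the analysis is finished, and an analysis plan not shown may assign the rules. Blinding makes it hard to steer the choice towards one arm. The defect remains because the protocol itself names these two rules, and both are unsuitable as the primary method for GOS.

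**Unseen schedule.** Table 2 is not shown, so an earlier GOS visit cannot be excluded. An acute-phase GOS in patients enrolled with GCS 6 to 12 would probably be poor, so carrying it forward would act much like worst-category scoring.

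**Deaths.** A reader might infer that deaths are treated as missing. For GOS nothing says so: category 1 already lies within poor recovery. For GCS and MBI the text is silent, so the risk is possible rather than stated.

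**Conclusion.** The point holds as a should-fix. On the text, last observation carried forward cannot fill a missing 6-month GOS, and at 12 months it assumes no change since 6 months. Worst-category scoring makes the result depend on retention. The bias has no predictable sign: it goes against whichever arm loses more.

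At the planned 10% overall loss, with 65% good recovery in both arms, the chi-squared type I error runs from about 5% with equal loss, through 6.0% at 8% versus 12%, to 9.5% at 5% versus 15%. Equal loss still costs about 8 points of power at the design rates. These sizes rest on assumed loss by arm, an assumed common recovery rate, loss unrelated to outcome, and the worst-category reading.

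**What to change.** In section 2.10, replace the sentence on last and worst observation carried forward with the following:

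- **Primary method for GOS.** All randomised patients are analysed, with multiple imputation of missing GOS from a small model: arm, randomisation strata, day-28 GCS or MBI, and the other GOS visit. The model must stay small because only about 4 patients per arm are expected to be missing. Deaths stay as observed GOS 1.
- **Sensitivity analyses only.** Worst-category imputation, with the term defined, and a tipping-point analysis.
- **GCS and MBI.** State that a score recorded before death is not carried forward, and give deaths the worst rank in a rank-based comparison.

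The cost is a protocol revision, which section 2.11 (Quality control) requires the ethics committee to approve, and modest analysis work. No new data are needed.

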Although effective therapeutic approaches for TBE remain limited, researchers continue to make meaningful attempts to determine effective and alternative treatment options, such as acupuncture for TBE. For patients who are unconscious after TBI, acupuncture may improve the Glasgow Coma Scale (GCS) score^[8,9]^; increase wake-promoting rates (Wake-promoting rates refers to the percentage of patients who recovered to GCS 15 to the total number of patients in this group at the end of treatment.)^[10,11]^; and change the GOS grade,^[12]^ which improves the prognosis. However, studies conducted previously by our team have demonstrated the fact that acupuncture could promote the absorption of traumatic intracerebral hematoma and brain contusion lesions, and improve the quality of life of such patients.^[13,14]^ Even though the acupuncture has been observed to be an effective treatment for patients with TBI, some of the acupuncture data remain weak and unconvincing.^[15]^ Few studies have investigated acupuncture as an adjuvant therapy in the acute phase of TBI (within 2 weeks after injury), which high-quality randomized controlled trials (RCTs) are particularly lacking.^[16]^ For this reason, and taking into account the preliminary results of the previous trials, a standardized RCT is planned to assess the effect of acupuncture on the prognosis of patients with TBE. The method of monitoring and quantitatively analyzing brain edema based on head computed tomography (CT) can be very convincing, and complementary acupuncture treatment in the acute-phase TBI (starting within 72 hours after injury) can be a novel idea of designing in this clinical trial.

If TBE is not controlled, the ICP will continue to increase, which can lead to fatal brain herniation.^[6]^ This unfavorable prognosis of TBE emphasizes the importance of managing the increased ICP in patients with TBE. Although the technology of ICP monitoring is precise and accurate, its invasive operation possibly harms patients.^[17]^ As a noninvasive examination for TBI, CT scans play a vital role in the study of brain edema; the CT images can evaluate ICP at an acute phase TBI, and software is used to reduce the subjectiveness of quantifying brain edema.^[18,19]^

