The pathological mechanism of TBE is unclear. After injury, the neuroinflammatory cascade that is considered an important mechanism of TBE promotes the rapid progression and progressive aggravation of TBE.^[20]^ Highly expressed inflammatory factors in the damaged brain tissue [e.g., C-reactive protein (CRP) and interleukin-6 (IL-6)] are released into the blood circulation; then, the degree of nerve tissue damage and the prognosis can be judged according to the serum levels of inflammatory factors.^[21]^ Many clinical studies have provided evidence of the anti-inflammatory effects of acupuncture. For example, Chen et al^[22]^ have concluded that acupuncture could downregulate the levels of inflammatory factors (IL-6 and IL-8) in patients with TBI, whereas Cho et al^[23]^ have found that acupuncture could reduce CRP levels in patients after craniotomy.

TBE is a complex and changeable pathological process, and the appropriate target cohort of treatment should be selected in order to measure the effectiveness of acupuncture. Here, we present the study protocol for a RCT to examine whether complementary acupuncture on acute-phase TBI is effective compared against the conventional treatment alone in patients with TBE. In addition, the study will also observe whether acupuncture is associated with an anti-inflammatory effect and a reduction in the volume of brain edema.

We present the following article in accordance with the SPIRIT reporting checklist.

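### Section 2.10 applies last or worst observation carried forward to all outcome data, including oedema volume, CRP and IL-6, where it can create or hide a treatment difference if the markers change between visits and missing visits differ by arm

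*Protocol article*

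**What the plan says.** Section 2.10 (Statistical analysis) sets one missing-data rule: "The data used will include the method of the last observation carried forward or the method of the worst observation carried forward". The next sentence ties it to the analysis population: "That is, this study will analyze the data with the full analysis set". The rule is not limited by outcome, visit or reason for missingness, and nothing says when the last value is used and when the worst.

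Section 2.6.2 (Secondary outcomes) has oedema volume, CRP and IL-6 "measured at four different time points (baseline and days 7, 14, and 28 after treatment". Section 2.10 says that these three outcomes "will be compared using either a generalized linear mixed model or the *t* test".

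The Introduction calls the first two weeks after injury the "acute phase of TBI (within 2 weeks after injury" period. It describes an inflammatory cascade that "promotes the rapid progression and progressive aggravation of TBE", and adds that "TBE is a complex and changeable pathological process". Section 2.9 allows for 10% loss during follow-up, not split by arm or by visit.

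**The concern.** For a living patient with no day-28 scan or sample, the rule supplies a value from day 14, day 7 or baseline, or the worst of them. Those visits lie in or close to the period that the Introduction calls acute. If the marker has moved since then, the filled-in value is wrong by the amount of that movement. Where one arm has more such patients, the errors do not cancel between arms, and part of the reported difference comes from the imputation rule. Filled-in values also enter the test as if they had been observed.

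These three outcomes carry the trial's stated aims of showing an anti-inflammatory effect and a reduction in oedema. The mixed model named in the same section can use every observed visit without filling any in, so the rule is not needed for them.

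**Working it through.** **The plan's own figure.** With 80% v 50% good recovery, two-sided 0.05, power 80% and unpooled variance, n = (1.960 + 0.842)² × (0.8×0.2 + 0.5×0.5) / 0.3² = 7.85 × 0.41 / 0.09 = 35.8, so 36 per group. Then 36 / 0.90 = 40 per group, 80 in total, as section 2.9 states. That figure rests on dichotomized GOS, and this point does not touch it. It supplies the 40 per arm and the 10% loss used below.

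**Assumptions, none of them in the protocol.** SD 1 at each visit; correlation 0.6 between visits; means at baseline, day 7, day 14 and day 28 of 0, −0.4, −0.8, −1.6 SD (full fall) or half of that, 0, −0.2, −0.4, −0.8 SD (half fall); day 28 missing, unrelated to the values; day-14 value carried forward; t test at day 28.

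**Bias with no true effect** (study minus control; d is the share missing at day 28):

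- Last value: (d_study − d_control) × (mean at day 14 − mean at day 28).
- Worst value: (d_study − d_control) × (expected highest of the three earlier values − mean at day 28). By simulation that expected highest value is 0.24 SD for the full fall and 0.36 SD for the half fall.

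At 15% v 5% (6 v 2 patients of 40):

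- Last value: 0.10 × 0.8 = 0.08 SD (full); 0.10 × 0.4 = 0.04 SD (half).
- Worst value: 0.10 × (0.24 + 1.6) = 0.18 SD (full); 0.10 × (0.36 + 0.8) = 0.12 SD (half).

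False-positive rates come from simulation. Ranges cover the two falls and the small differences between repeated runs.

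| Missing at day 28 | Last value: bias, false positives | Worst value: bias, false positives |
|---|---|---|
| 10% v 10% | 0 SD, 5% | 0 SD, 5% |
| 15% v 5% | 0.04–0.08 SD, 5–6% | 0.12–0.19 SD, 7–11% |
| 30% v 10% (12 v 4 patients) | 0.08–0.16 SD, 6–10% | 0.23–0.37 SD, 14–26% |

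Observed day-28 values alone give bias of about 0 and about 5% false positives in every row. Exchanging the arms reverses the sign of the bias.

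**True benefit of 0.5 SD at day 28, full fall, 15% missing in the study arm v 5% in controls.**

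- Last value. Controls: 0.95 × (−1.6) + 0.05 × (−0.8) = −1.56. Study arm: 0.85 × (−2.1) + 0.15 × m, where m is its day-14 mean. If 0.25 to 0.5 SD of the benefit is present by day 14, m is −1.05 to −1.30 and the arm mean is −1.94 to −1.98. The estimated benefit is 0.38 to 0.42 SD, about 0.40.
- Worst value: about 0.26 SD by the same reasoning.
- Observed values: 0.50 SD.

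**Sensitivity to the assumed scale.** Let the SD be 50% of each visit mean, with 15% v 5% missing. Markers falling by 80 to 90% then give 13 to 21% false positives under the last-value rule. A slower fall (100, 90, 75, 60) gives 5.4 to 7.0%, and a nearly flat course (100, 95, 90, 85) about 5%. The size therefore depends on a trajectory that the protocol does not give.

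**The case against.** The strongest objection concerns size. The only loss figure is 10%, and it covers follow-up to 12 months, so 30% v 10% by day 28 exceeds the plan's own allowance. Around 10%, last-value bias is small unless the arms differ sharply, and with equal loss and no effect it is nil. Section 2.10 also continues collection after treatment is interrupted, which reduces missing visits. All of this stands, and the 30% v 10% row should be read only as an extreme.

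A reader might infer that the markers are known to change fast and fall by day 28. The documents do not support that. The remark on changeability concerns oedema and introduces the choice of cohort. The remark on rapid progression describes worsening. Neither gives a course for CRP or IL-6.

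A reader might also infer which arm would lose more visits. Unblinded participants, relatives' right to withdraw and reliance on routine records make imbalance possible, but no discharge or drop-out figures by arm are given. Faster recoverers leaving early and control families leaving early would push in opposite directions.

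Nor does section 2.10 say that values are filled in before the mixed model is fitted. It leaves the order open and allows a t test instead. The calculation above tests a t test after filling, not the mixed model or the nonparametric option.

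Finally, outcome-specific rules are often left to the analysis plan. Here, however, the protocol states a rule, and states it for all outcomes.

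**Conclusion.** The point holds for oedema volume, CRP and IL-6. The stated rule covers them, is biased whenever the marker moves and missingness is unequal, and is unnecessary given the model already named. Under the assumed falls of 0.8 to 1.6 SD and loss near the plan's 10%, the last-value effect ranges from nothing to slight. The worst-value effect is more than twice as large at 15% v 5%, and the protocol does not say which rule governs. At the same imbalance, a real 0.5 SD benefit could be reported as about 0.40 or 0.26 SD. Size and direction in the actual trial cannot be stated, because the trajectory, correlation and missingness by arm are all assumed. It would be wrong to conclude that the primary result is compromised: the point concerns secondary outcomes in living patients only. It is worth correcting, but not a threat to the trial's main conclusion.

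**What to change.** In section 2.10, state that carry-forward is not used for oedema volume, CRP and IL-6. Analyse all observed day-7, day-14 and day-28 values with the mixed model already named, with terms for group, visit, group-by-visit and the baseline value, and with no imputation beforehand. Remove the t-test alternative for these three outcomes. If last-value carry-forward is kept, label it a sensitivity analysis.

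The cost is wording in the protocol or analysis plan; no new data or patients are needed. The downside is that the model assumes missingness depends only on observed values, which a sensitivity analysis for departures from that assumption can probe.

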## Abstract

**Background::**

Traumatic brain edema occurs commonly brain injury, and most manifests as pericontusional edema of brain contusions. On the basis of evidence-based medicine, apart from recommending craniotomy and mannitol, there are few particularly effective measures to prevent and treat traumatic brain edema. It is uncertain whether an early complementary acupuncture treatment would improve long-term outcomes of patients with traumatic brain edema. The aim of this study is to assess the efficacy and the safety of early complementary acupuncture for patients with traumatic brain edema.

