#### Safety assessment

2.6.3

Safety will be assessed by monitoring adverse events. Any adverse events or abnormalities that may occur in this study, including bleeding, local hematoma, infection, pallor, sweating or dizziness, fainting during acupuncture treatment, and objective worsening of existing symptoms, will be voluntarily reported and documented on case report forms (CRFs). The CRFs will record the adverse events in detail, including the time and date of occurrence, degree of severity, any measurement related to the treatment of the event, and any potentially causal relationship between the treatment and the event. If any severe adverse event occurs, acupuncture intervention will be ceased immediately, and the principal investigator will be informed and will take proper actions. It is required to report the events and actions that have occurred to the ethics committee of the hospital.

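### Safety is an aim, but the only between-group analysis stated for it is a test of adverse event rates at P < .05, which cannot show how much excess harm is excluded in a trial sized on GOS alone

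*Protocol article*

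**What the plan says.** The Abstract (Background) sets two aims: "The aim of this study is to assess the efficacy and the safety of early complementary acupuncture for patients with traumatic brain edema". Section 2.6.3 (Safety assessment) says how safety data arise: "Safety will be assessed by monitoring adverse events", with details of each event recorded on case report forms.

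Section 2.10 (Statistical analysis) fixes the comparison: "GOS, wake-promoting rates, and adverse events rates will be compared using the chi-squared" or Fisher's exact test. The threshold is general: "For all analyses, the results with a *P* value less than .05 will be considered statistically significant". A confidence interval is named for two other outcomes: "GCS and MBI scores will be compared between the 2 groups by *t* test with a 95% confidence interval". None is named for adverse events. Section 2.10 also says that categorical variables will be summarised as counts and percentages.

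Section 2.9 (Sample size calculation) sizes the trial on good recovery by GOS, 80% against 50%. It gives no adverse event rate, no difference in adverse events that would matter and no margin.

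**The concern.** A significance test of adverse events answers whether the data contradict equal rates. The safety aim needs a different answer: how large an excess under acupuncture remains compatible with the data. When a trial is sized for a 30-point efficacy difference, a moderate excess of adverse events will often give P > .05, and that result does not separate little harm from little information.

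The patients are acutely brain-injured, some of them after craniotomy, and the Discussion says the study could change recommendations for acute-phase acupuncture. A reader weighing that claim needs the size of harm that the data leave open, and the stated safety comparison does not supply it.

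**Working it through.** **Step 1. Reproduce the plan's own figure.** Inputs from section 2.9: 80% vs 50%, two-sided alpha 0.05, power 80%, 10% loss. With the unpooled normal formula:

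n = (1.960 + 0.842)² × (0.5×0.5 + 0.8×0.2) / 0.30² = 7.849 × 0.41 / 0.09 = 35.8, so 36 per group.

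36 / (1 − 0.10) = 40 per group, 80 in total. This matches the protocol and confirms that adverse events played no part in the size.

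**Step 2. Power of the adverse event test.** The protocol gives no event rates, so those below are assumptions. For control rate p_C and acupuncture rate p_A, power is the sum, over all pairs of counts with P < .05, of Bin(a; 40, p_A) × Bin(b; 40, p_C). This is exact enumeration with two-sided tests, the chi-squared test uncorrected, counting rejections in either direction.

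| Control vs acupuncture | Chi-squared | Fisher |
|---|---|---|
| 5% vs 10% | 15% | 4% |
| 5% vs 15% | 35% | 18% |
| 5% vs 20% | 57% | 41% |
| 10% vs 20% | 25% | 16% |
| 10% vs 25% | 44% | 33% |
| 10% vs 30% | 63% | 53% |
| 20% vs 40% | 50% | 41% |
| 30% vs 60% | 80% | 72% |
| 15% vs 45% | 85% | 79% |
| 0% vs 15% | 87% | 57% |

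On a grid of whole percentages, the acupuncture rate at which power first reaches 80% (chi-squared/Fisher) is 27%/30% against 5%, 36%/38% against 10% and 50%/52% against 20%. These are excesses of 22 to 32 points. At 36 per group power is lower still: 32%/15% for 5% vs 15%.

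**Step 3. What an interval adds.** Suppose 6/40 events under acupuncture and 2/40 in controls. Fisher P = 0.26 and chi-squared P = 0.14, so neither is significant. The risk difference is 0.15 − 0.05 = +0.10. The Wilson limits are 0.071 to 0.291 for 6/40 and 0.014 to 0.165 for 2/40. The Newcombe 95% limits are then:

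- lower: 0.10 − √[(0.150 − 0.071)² + (0.165 − 0.050)²] = −0.040
- upper: 0.10 + √[(0.291 − 0.150)² + (0.050 − 0.014)²] = +0.245

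The test reports no significant difference. The interval shows that an excess of 24 points is still compatible with the data.

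**Step 4. Events that only needling can cause.** Section 2.6.3 lists fainting during a treatment session, which cannot occur in a control patient. For such events a between-group test tells little, while a within-arm limit is informative. With 0/40 events the exact two-sided 95% upper limit is 1 − 0.025^(1/40) = 8.8%.

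**The case against.** The case against is substantial, and it rules out several stronger readings.

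- *A reader might infer that the protocol treats P > .05 as proof of safety.* No passage says so. The .05 rule only defines statistical significance.
- *A reader might infer that the test is the only safety rule.* It is not. Counts and percentages will be reported. Section 2.6.3 requires severity and possible causality to be recorded, acupuncture to cease after a severe event, and the ethics committee to be told. Section 2.5.3 gives discontinuation conditions, and sections 2.8 and 2.11 provide an independent monitoring board. However, these act on individual patients and on conduct, and percentages carry no measure of uncertainty. None of them says how much excess harm the final data exclude.
- *A reader might infer that most relevant harms, or most doublings and triplings, would be missed.* The documents define no relevant harm and give no rates. Step 2 shows that power depends heavily on the control rate: a tripling from 10% or 15%, or a doubling from 30%, would be detected more often than not.
- *An interval may stand in a statistical analysis plan that is not shown.* True, and its absence here would be a weak point alone. The point concerns what section 2.10 does state, namely a test as the safety comparison.
- *Low power for adverse events is usual, and the trial is modest about itself.* Sizing on the primary outcome is normal, and the Discussion calls the trial a feasibility study with few cases that could supply pilot evidence. That lowers the priority. It also favours estimation over testing.

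The test is a valid method for comparing two rates and need not be removed.

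**Conclusion.** The point holds in a limited form: the stated method is poorly suited to the stated safety aim. If control rates are about 5% to 10%, the test has 4% to 35% power against excesses of 5 to 10 points. Power rises to between 53% and 85% for 10% vs 30% and 15% vs 45%. All these figures rest on assumed rates and 40 evaluable patients per group. What does not depend on the assumed rates is that a P value alone cannot state which excess is excluded. This is a cheap improvement and not a flaw that invalidates the trial.

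**What to change.** In section 2.10:

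- Report adverse events, and severe adverse events separately, as number and percentage per group with the risk difference and its 95% confidence interval (for example Newcombe). Make this the main safety analysis. The chi-squared or Fisher test may stay beside it.
- For events possible only with needling, report the rate in the acupuncture arm with an exact upper confidence limit, including when no event is seen.
- State that the safety conclusion will be drawn from the interval, and that a non-significant difference is not evidence of safety.

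The change is to wording and output only, with no extra patients or data. Its cost is a less favourable safety statement, because at this size the intervals will be wide and will often leave sizeable excesses open.
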